Our group has employed such a strategy to identify food-specific compounds (FSCs) that are detected in biospecimens, associate with intake of that food, and are associated with cardiometabolic health indicators [11–13]. Our findings suggest that several foods consumed within complex healthy dietary patterns such as the Dietary Approaches to Stop Hypertension (DASH) and MED diets have novel food-specific signatures [11–13]. To date, we have conducted metabolomics analyses of over 100 foods to identify compounds uniquely present in these foods. Using the established platform and methodology developed by our team [14, 15], we have identified thousands of distinct compounds within individual foods present in a MED dietary pattern [16], demonstrating our ability to use our approach to define FSCs and suggesting these FSCs may be further explored as biomarkers of food intake. The relationships between these biomarkers of food intake and health effects can then elucidated.

In addition to identifying FSCs from individual foods, we have shown that these compounds are present in biospecimens such as blood and urine from individuals who have consumed these foods as part of a fully controlled feeding intervention [11, 13]. These results suggest FSCs are discernable in biospecimens after consumption of complex meals within overall dietary patterns and thus may be useful as putative biomarkers of food intake [17]. We have also demonstrated the ability to link observed FSCs in plasma with clinical indicators, suggesting food compounds may be associated with a biologic effect (i.e., putative biomarkers of effect) [11]. For example, the MED intervention improved participant systolic and diastolic blood pressures, and plasma/serum total cholesterol, triglycerides, and LDL cholesterol [16]. Results from our analyses identified FSCs that are associated with improvement in one or more of these cardiometabolic health indicators. These promising results warrant follow-up to confirm findings in an independent cohort.

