Our results support the use of unmetabolized FSCs in either plasma or urine as candidate biomarkers of food intake. However, evaluation of multiple biospecimen types (e.g., blood and urine) simultaneously may increase coverage by collecting complementary information about different aspects of food metabolism [18]. Thus, collection and analysis of multiple biospecimen types will provide more comprehensive compound lists to define metabolomic signatures for testing associations with health indicators. Our preliminary results need to be prospectively tested within an independent intervention, a necessary next step for evaluation of reproducibilty and potential validation as biomarkers of food intake. Notably, our previous nutrimetabolomics research has been conducted within fully controlled feeding trials, making it difficult to elucidate the effects of incremental shifts between an “unhealthy” habitual/Western dietary pattern toward “healthy” evidence-based dietary patterns such as DASH or MED. The current mini-MED clinical trial study design and extensive biospecimen sampling plan directly address these limitations.

We are conducting a 16-week randomized, multi-intervention, semi-controlled feeding study among individuals with overweight/obesity who do not habitually consume a MED dietary pattern to comprehensively evaluate the reproducibility of FSCs using our innovative nutrimetabolomics approach. The novel FSCs identified in our eight MED target foods will be evaluated in participant biospecimens to assess change after intervention and to validate associations with cardiometabolic health indicators in this prospective semi-controlled feeding trial. The overall scientific premise is that FSCs will be reproducibly found when individuals consume specific foods, will not be found when individuals do not consume those foods, and will be associated with beneficial indicators of cardiometabolic health. In addition, we will evaluate the reproducibility of FSCs from beef in the context of different backgrounds (MED vs habitual/Western foods). Based upon existing literature, exploratory analyses will also be conducted to identify shifts in microbiome structure/function in response to incremental dietary changes.

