### Trial design {8}

This trial is a 16-week randomized, multi-intervention, semi-controlled feeding study of Mediterranean-amplified (mini-MED) and habitual/Western-style (Western) isocaloric dietary interventions containing 500 kcal/day from target foods. Participants are randomized (1:1) to start either the mini-MED or the Western dietary intervention, with subsequent assignment to the other upon completion of the first. Each 4-week intervention (mini-MED and Western) is repeated once. The Western intervention serves as both a washout of the mini-MED foods and a negative control for the postprandial response when the mini-MED foods are not consumed. Within the mini-MED arm, participants are further randomized to first receive salmon (mini-MED salmon) or lean, unprocessed beef (mini-MED beef) as a protein source, with consumption of the alternate protein source in their second mini-MED intervention period (Fig. 1). Outcome measures and biospecimen sampling take place at baseline and intervention weeks 4, 8, 12, and 16, and outcomes will be assessed using an exploratory approach.

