## Statistical methods

### Statistical methods for primary and secondary outcomes {20a}

Assessment of the primary outcome of change in FSCs will be completed using the intercept of linear mixed effects models (LMMs) with change in FSCs (post–pre) as the outcome and a random intercept to control for repeated measures. Analysis will be stratified by mini-MED and Western interventions since we expect FSCs to increase during the mini-MED arm and to decrease during the Western arm. FSCs that significantly increase during the mini-MED interventions and significantly decrease during the Western interventions will be considered validated. We will adjust for multiple testing using false discovery rate (FDR) for the number of FSCs [37]. We will complete stratified analysis by intervention period to assess reproducibility of FSCs in increase (mini-MED) and decrease (Western). The relationship between cardiometabolic health indicators and diet intervention will be assessed using LMMs similar to that described above. The relationship between cardiometabolic health indicators and FSCs will be assessed using LMMs over all intervention periods with an interaction term for FSCs and diet (i.e., mini-MED, Western) to capture differential effects by diet.

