Data for exploratory outcomes related to the gut microbiota will be evaluated to assess (1) change over dietary intervention, (2) association with cardiometabolic health indicators, and (3) descriptive differences between upper GI and stool microbiota. Data will be presented as sequence count data. For both 16S rRNA gene amplicon and metagenomic datasets, taxa or genes that differ in abundance or prevalence between intervention groups and pre- to post-intervention will be identified by negative binomial mixed effects regression, with the total sequence count for each subject as a covariate [38]. Similarly, associations between gut microbiota variables and continuous cardiometabolic health indicator variables will be assessed using LMMs controlling for total sequence count. Permutation-based analysis of variance (PERMANOVA) tests using common beta-diversity indices (e.g., UniFrac, Bray–Curtis) will assess between-group differences in overall microbial community structures. Exploratory analyses of gut microbiota data also will be performed using unsupervised ordination methods (e.g., principal coordinates analysis). Supervised classification methods (e.g., random forests) will be used to build models of cardiometabolic health indicators, with the goal of identifying particular microbial taxa, or host factors, that best predict the cardiometabolic health indicators. To control for multiple testing for FSCs, cardiometabolic health indicators, and microbial taxa/genes, we will use an FDR correction [37].

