## Discussion

This will be the first study to prospectively assess FSCs identified via metabolomics analysis of a completed MED controlled feeding intervention in an independent cohort. FSCs from target foods consumed within a complex background habitual dietary pattern will be assessed as putative biomarkers of intake to these foods as well as explored as potential biomarkers of effect by examining associations with cardiometabolic health indicators and microbiome community structure and function. This will achieve the important step of validation of FSCs for a large panel of foods within a complex dietary background which, to our knowledge, has not been performed. Such evaluation is critical for the rigorous development and testing of dietary biomarkers and will catalyze the advance in knowledge of the role of dietary patterns, specific foods, and individual compounds on the physiology of metabolic health outcomes. Strengths include a rigorously designed randomized, multi-intervention dietary intervention with provision of target foods of interest to encourage participant adherence. Frequent and intentional sampling of multiple biospecimen types (blood, urine, stool) aligning with dietary intake data and clinical assessments will allow for detailed assessment of the relationships between dietary intake, FSCs, and cardiometabolic health indicators.

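### The article promises to validate earlier FSC-indicator associations, but its analysis neither tests those pairs separately nor says what would count as replication

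*Protocol article*

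**What the plan says.** In Background and rationale {6a}, the article reports from the completed MED trial: "Results from our analyses identified FSCs that are associated with improvement in one or more of these cardiometabolic health indicators". It adds: "These promising results warrant follow-up to confirm findings in an independent cohort". It then says the FSCs will be evaluated here "to validate associations with cardiometabolic health indicators in this prospective semi-controlled feeding trial", on the premise that they "will be associated with beneficial indicators of cardiometabolic health". That premise has a direction.

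In Statistical methods {20a}, the matching analysis is one sentence. It begins "The relationship between cardiometabolic health indicators and FSCs will be assessed using LMMs over all intervention periods" and adds an FSC-by-diet interaction. Multiplicity is covered by: "To control for multiple testing for FSCs, cardiometabolic health indicators, and microbial taxa/genes, we will use an FDR correction". No earlier pair, expected sign or success rule is given for associations. The same section does give a directional validation rule for FSC change: a significant rise on mini-MED and a significant fall on Western.

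Two other places describe the work differently. Trial design {8} says "outcomes will be assessed using an exploratory approach". The Discussion says FSCs will be "explored as potential biomarkers of effect by examining associations with cardiometabolic health indicators". The aims and hypotheses in Objectives {7} do not include FSC-indicator associations.

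**The concern.** A replication question concerns a known list: did the pairs found before appear again, with the same sign? The stated analysis is built for a different question, namely which FSCs relate to which indicators. Two things follow.

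First, three results are not distinguished by any stated rule: an earlier pair that replicates, a pair never seen before, and an earlier pair that is significant with the opposite sign.

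Second, if the earlier pairs are corrected together with many pairs that have no prior evidence, they face a stricter threshold than the validation question requires. In a trial planned for 20 completers, that can decide whether a real association is confirmed.

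**Working it through.** **Plan's own figure.** There is none to reproduce. Sample size {14} gives power only for change in FSCs by paired *t*-test, not for associations.

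**Counts from the article**
- Plasma FSCs in Table 1 for the seven mini-MED plant foods: 30 + 136 + 27 + 112 + 23 + 17 + 10 = 355, which matches the 355 in Sample size {14}.
- Adding salmon and beef: 355 + 143 + 76 = 574.
- Cardiometabolic indicators named in Outcomes {12}: 8. All FSCs by all indicators: 574 × 8 = 4,592.

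**Possible FDR families.** Correction across FSCs within each indicator gives about 355-574 tests. Correction across FSCs and indicators together gives up to 4,592.

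**Assumptions (none is in the article).** Benjamini-Hochberg (BH) at 5%, two-sided, independent tests; 10-20 earlier pairs, half of them real; within-person partial correlation *r* of 0.4 or 0.5; 58 residual df (20 people × 4 periods = 80 changes, less 20 participant means, less 2). The FSC-by-diet interaction is not modelled.

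**Formula.** Each real pair has a *t* statistic on 58 df with noncentrality *r*/√(1 − *r*²) × √58:
- *r* = 0.4: 0.436 × 7.62 = 3.32
- *r* = 0.5: 0.577 × 7.62 = 4.40

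**Why the family matters.** The BH cut-off with *k* discoveries among *m* tests is 0.05*k*/*m*. Suppose 5 of 10 earlier pairs are real and they are the only discoveries:
- own family of 10: 0.05 × 5/10 = 0.025
- 355 tests: 0.25/355 = 0.00070
- 574 tests: 0.25/574 = 0.00044
- 4,592 tests: 0.25/4,592 = 0.00005

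**Simulated chance that a real earlier pair is significant**

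| Family | *r* = 0.4 | *r* = 0.5 |
|---|---|---|
| Earlier pairs only | about 83% | 98% |
| 355-574 FSCs | about 25-62% | about 69-93% |
| 4,592 pairs | about 12-60% | about 49-92% |

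The low ends apply when nothing outside the earlier list is real. The high ends apply when about one in ten of the other pairs is real, because more discoveries loosen the BH cut-off.

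**Sensitivity to the amount of information.** A separate check used 10 earlier pairs, all real, at *r* = 0.5. It compared a one-sided family of those 10 with two-sided screens of 21 × 8 = 168 and 355 × 8 = 2,840 tests:
- 40 effective observations: 95%, against 59% and 25%
- 80 independent observations, the most favourable case: 100%, against 97% and 85%

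Part of this gap comes from the one-sided test. The loss shrinks when correlations are strong and the period changes are nearly independent.

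**The case against.** The strongest reply is that the article is silent rather than wrong. It does not say that every FSC is tested against every indicator in one family, nor that the tests ignore direction. A reader might infer both, but the text supports neither. Objectives {7} speaks of FSCs defined in advance, the only family size stated in {20a} is the number of FSCs, and the compound filters in {20c} would lower the Table 1 counts. With only 21 FSCs in a family, 5-10 of them real, power at *r* = 0.4 is 75-82%, close to the 83% of a dedicated family. A list of pairs and a replication rule could also sit in an analysis plan that is not shown. All of this stands, and it is why the power figures are illustrative.

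A reader might also infer that the earlier associations will mostly fail to confirm. That does not follow: at *r* = 0.5 most readings leave power above one half. Nor would replication be impossible to judge, since new estimates can be set beside the earlier results after the fact. What the article lacks is a rule fixed in advance.

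Finally, Trial design {8} and the Discussion call this work exploratory, and an FDR screen suits that status. This does not remove the point. The background still promises confirmation and validation, so the article gives the same analysis two purposes. {20a} also shows that a directional validation rule was thought worth stating for FSC change.

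**Conclusion.** The concern holds in a limited form. The background commits the trial to confirming and validating earlier FSC-indicator associations, two other sections call the work exploratory, and {20a} supplies only a general mixed model with an FDR correction. That conflict, and the absence of any stated criterion for a validated association, can be read from the text without assumed numbers.

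The loss of power is conditional. Under the assumptions above, every family of 355 tests or more gave a real earlier pair less chance than a family of its own. At *r* = 0.4 the loss is roughly 20 to 70 percentage points (83 − 62 = 21; 83 − 12 = 71). At *r* = 0.5 it is roughly 5 to 50 (98 − 93 = 5; 98 − 49 = 49). The number of earlier pairs, the share that is real, the correlations and the independence of tests are all assumed. This is a worthwhile, cheap improvement to a non-primary analysis and does not affect the primary outcome.

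**What to change.** In Statistical methods {20a}:
1. Before assay data are released, freeze the list of FSC-indicator pairs found in the completed MED trial, each with its sign. The article plans batch assays at study completion {33}, so this was still possible at the version shown.
2. Test these pairs as their own FDR family.
3. Call an association validated only if it is significant with the earlier sign, and say which coefficient of the FSC-by-diet model carries that sign.
4. Analyse all other pairs as a separate exploratory FDR family and report them as hypothesis-generating.

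If the sponsor prefers to keep the work exploratory, the alternative is to drop *confirm* and *validate* for associations in Background and rationale {6a}.

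The cost is one paragraph and a list taken from the sponsor's own earlier results, with no new data. The small downside is that pairs outside the list can only generate hypotheses.

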### Outcomes {12}

The primary outcome for this clinical trial is change in the relative abundance of FSCs from beginning to the end of each dietary intervention period in participant plasma samples. Secondary outcomes include detection of FSCs in participant urine samples as well as mean changes in cardiometabolic health indicators (e.g., total cholesterol, LDL cholesterol, HDL cholesterol, triglycerides, insulin, glucose, systolic and diastolic blood pressure), inflammatory markers (e.g., C-reactive protein, interleukin-6, tumor necrosis factor-alpha, alpha-1-acid glycoprotein), and adipokines (e.g., leptin, adiponectin) over each dietary intervention. Exploratory outcomes include changes in diversity and community composition of the gut microbiota over each dietary intervention period.

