#### Sample size {14}

Most of our planned analyses use each individual as their own control by looking at the change over each dietary intervention period. This reduces between subject variability compared to a cross-sectional analysis and increases the statistical power at a given sample size. To obtain a reasonable minimum expected effect size for the mean difference divided by the standard deviation of the difference (i.e., Cohen’s *d* effect size), we used our analysis of salmon FSCs [13]. The minimum salmon FSC effect size that passed an FDR adjustment was 0.45. Using a paired *t*-test after consuming the food, a sample size of *N* = 20 was needed to achieve 80% power for this effect size of 0.45 and a Bonferroni multiple testing adjustment for the number of compounds that increased in the preliminary MED data (*N*_compounds_ = 21; *p*-value_adjusted_ = 0.05/21 = 0.0024). We assume a 10% loss to follow-up based on our experience in similar dietary intervention trials and therefore enroll *n* = 22 eligible individuals to have *n* = 20 individuals complete the trial.

We also evaluated the power of *N* = 20 sample size further using the Bonferroni adjustment for the 21 compounds that increased after consumption of the preliminary Mediterranean diet foods (*p*_adj_ = 0.0024) and a stricter adjustment using all 355 compounds that were detected in the MED foods and plasma (*p*_adj_ = 0.05/355 = 0.00014). For both significance thresholds, we achieve power across a range of relevant effect sizes (Fig. 2) including nearly 100% power to detect an effect size of 0.75 (the median effect size for the salmon FSCs that passed the FDR threshold).

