### Assignment of interventions: allocation

#### Sequence generation {16a}

All participants complete the mini-MED and Western dietary interventions twice each for four total intervention periods. Participants are randomized (1:1) to start either the mini-MED or Western dietary interventions, with subsequent assignment to the other upon completion of the first. A second randomization within the mini-MED arm is conducted to allocate participants to order of consumption of either salmon or lean, unprocessed beef as a protein source resulting in a total of four possible intervention orders (Fig. 1). Lean, unprocessed beef is consumed as the protein source in both Western intervention periods. A permuted block randomization scheme and stratification by sex has been generated and is utilized to ensure balance between intervention order and number of males and females. The allocation sequence was generated using computer-generated random number sequence in R using the *sample* command in *base* R package.

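### Prevalence of taxa and genes is assigned to a negative binomial count model, which tests the mean count and does not test prevalence separately from abundance

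*Protocol article*

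**What the plan says.** The microbiota analysis is described under Statistical methods for primary and secondary outcomes {20a}. The data form is fixed first: "Data will be presented as sequence count data". For both the 16S rRNA gene and the metagenomic data, target and method are then fixed together: taxa or genes that "differ in abundance or prevalence between intervention groups and pre- to post-intervention will be identified by negative binomial mixed effects regression". Each subject's total sequence count enters as a covariate. This is the only method named for that target.

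The same section lists linear mixed models relating microbiota to cardiometabolic indicators, PERMANOVA on beta-diversity, ordination and random forests. None of these tests whether an individual taxon or gene is present more often under one diet, or after an intervention than before it. No presence/absence, hurdle or zero-inflated component is named.

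Outcomes {12} sets the status: "Exploratory outcomes include changes in diversity and community composition of the gut microbiota over each dietary intervention period". Multiplicity is covered in {20a}: "To control for multiple testing for FSCs, cardiometabolic health indicators, and microbial taxa/genes, we will use an FDR correction".

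**The concern.** Abundance and prevalence are different quantities. Prevalence is the share of samples in which a taxon or gene is found at all. Abundance is how much of it there is. The article names both as targets and gives both to a regression whose only diet effect acts on the mean count.

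A diet that makes a taxon appear in more people at lower counts can leave the mean almost unchanged and go unreported. When the mean does move, a significant coefficient does not tell the reader whether the taxon became more common, more plentiful where present, or both. At stake is the interpretation of the taxon-level and gene-level lists: the appearance or loss of organisms with diet is one of the two stated targets, and it gets no test of its own.

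**Working it through.** The article gives no power, prevalence, dispersion or effect size for the microbiota, so there is no stated figure to reproduce. The check has an algebraic part, which needs no assumed values, and a simulation, which does.

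**1. Algebra.** For a negative binomial count with mean μ and size k, the probability of a non-zero count is

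P(Y > 0) = 1 − (1 + μ/k)^(−k).

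At k = 1:
- μ = 1 gives 1 − 2^(−1) = 0.50
- μ = 5 gives 1 − 6^(−1) = 0.83
- μ = 20 gives 1 − 21^(−1) = 0.95

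Once k is given, prevalence is fixed by the mean. The regression has no second coefficient through which prevalence could move by itself.

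**2. Simulation inputs.**
- From Sample size {14}: 20 completers ("enroll *n* = 22 eligible individuals to have *n* = 20 individuals complete the trial").
- From Sequence generation {16a}: each diet is given twice ("All participants complete the mini-MED and Western dietary interventions twice each for four total intervention periods"), hence two pre and two post samples per participant for one diet.
- Assumed: a presence probability for each sample, independent within participant; a positive count when present, with size 2; a participant effect on abundance with SD 0.5 on the log scale; equal sequencing depth; two-sided 5% level; 1,000 runs per scenario.
- Tests compared: negative binomial regression of the mean count with participant-clustered standard errors, standing in for the mixed model; and a paired test on presence/absence.

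Mean count = prevalence × mean count when present.

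| Scenario | Mean count, pre → post | Negative binomial | Presence/absence |
|---|---|---|---|
| No change (0.5; 40 when present) | 20 → 20 | 6.8% | 5.8% |
| Prevalence 0.4 → 0.8, count when present 80 → 40 | 32 → 32 | 8.2% | 97.2% |
| Prevalence 0.3 → 0.9, count when present 90 → 30 | 27 → 27 | 8.7% | 100% |
| Prevalence 0.3 → 0.8, count when present 40 throughout | 12 → 32 | 76.0% | 99.5% |
| Prevalence 0.6 throughout, count when present 40 → 100 | 24 → 60 | 85.7% | 4.8% |

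**3. Reading the table.**
- *Offset shifts.* The Monte Carlo standard error of the difference between 8.2% and 6.8% is √(0.082×0.918/1000 + 0.068×0.932/1000) ≈ 1.2 percentage points, and it is about the same for 8.7%. The rejection rates of 8.2% and 8.7% therefore lie within about 1.6 standard errors of the null rate.
- *Shifts that move the mean.* The fourth row is flagged in 76.0% of runs, so the model is not blind to prevalence.
- *No separation.* The last two rows have similar mean ratios (32/12 = 2.67 and 60/24 = 2.5) and both are usually flagged. One is purely a prevalence change and the other purely an abundance change. The coefficient does not tell them apart; the presence/absence test does.

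**The case against.** The strongest case against has four parts.

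**The model can find prevalence shifts, sometimes better than a logistic model.** In a negative binomial with fixed dispersion, prevalence rises strictly with the mean. At k = 1, prevalences of 0.30 and 0.60 correspond to means of 1/0.70 − 1 = 0.43 and 1/0.40 − 1 = 1.50, a 3.5-fold change. With data generated from a negative binomial (20 people, two pre and two post samples, equal depth, known dispersion, k from 0.3 to 1, 300 runs each), a shift from 30% to 60% was found in 94-99% of runs by the count model and in 73-79% by a logistic model. Null rates were 7-9% and 4-6%. This stands. A reader might infer that the planned model cannot detect a prevalence shift, or that most such shifts would be missed. The documents do not support that: the result depends on how prevalence and abundance move together, and the article gives nothing from which to tell.

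**The offset scenarios are chosen.** They hold the mean exactly constant, so the count model has no signal by construction. This also stands. They show that such shifts are missed, not that they are common.

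**The wording may be a loose description of a screen.** The sentence promises to identify features that differ in either respect, not separate prevalence estimates. As a screen the model is partly suitable. But the sentence names the model for the prevalence target, so this is a mismatch between a stated target and a stated method, not detail left to a fuller document. The cited methods source was not available and has not been relied on.

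**The consequence is small.** The outcome is exploratory, FDR-corrected and outside the sample size calculation. This stands and sets the weight.

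**Conclusion.** The point holds in a limited form. Section {20a} gives abundance and prevalence to one regression on the mean count. That regression does not test prevalence separately and cannot distinguish a prevalence shift from an abundance shift; both statements follow from the form of the model.

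The size of the power loss is illustrative. It runs from near-total when higher prevalence is offset by lower abundance when present (8-9% against 97-100%), through moderate when abundance when present is unchanged (76% against 99.5%), to none or a reversal when the data are truly negative binomial. These rates rest on assumed prevalences, counts, dispersion and equal sequencing depth, and on clustered stand-ins for the mixed model.

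Nor does the point discredit the microbiota analysis as a whole: the negative binomial mixed model remains a reasonable choice for abundance. No primary or secondary conclusion depends on this, so it is a low-weight improvement.

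**What to change.** Keep the negative binomial mixed model and describe it as the analysis of abundance. For prevalence, add one sentence naming a mixed-effects logistic model of presence/absence for each taxon or gene, with a participant random intercept, diet and period effects, and the log sequencing depth of the sample as covariate, under FDR control.

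The alternative is to delete the reference to prevalence, so that the stated target matches the model.

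The cost is one sentence and one more model per feature, with no new data collection. Plans for collection, laboratory evaluation, and storage of biological specimens {33} schedules batch analyses at study completion for primary and secondary outcomes, and Biospecimen sampling {18a} does so for stool. Trial status reports recruitment as ongoing, so as of this version the change could be written down before the stool results exist. The downsides are a second set of exploratory tests with about 20 participants, and logistic fits that may be unstable for very rare or near-universal taxa.

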### Additional consent provisions for collection and use of participant data and biological specimens {26b}

All enrolled participants provide blood, urine, and stool samples at the five in-person data collection visits conducted at baseline and intervention weeks 4, 8, 12, and 16. Data are stored and biospecimen samples are banked for unspecified future research.

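### Sequencing depth is defined per subject although each participant gives five stool samples, so it cannot adjust within-person contrasts; the PERMANOVA also needs a rule for repeated samples

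*Protocol article*

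**What the plan says.** Section {20a} of the protocol article gives three inferential analyses of the gut microbiota that matter here.

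- Taxa and genes differing between interventions or from before to after a period "will be identified by negative binomial mixed effects regression, with the total sequence count for each subject as a covariate".
- Associations between microbiota variables and continuous cardiometabolic indicators "will be assessed using LMMs controlling for total sequence count". This sentence does not say whether the count is per subject or per sample.
- PERMANOVA "tests using common beta-diversity indices (e.g., UniFrac, Bray–Curtis) will assess between-group differences in overall microbial community structures". The groups, the time points and the permutation scheme are not stated.

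On the data, section {26b} says participants "provide blood, urine, and stool samples at the five in-person data collection visits conducted at baseline and intervention weeks 4, 8, 12, and 16". On the design, section {16a} says "All participants complete the mini-MED and Western dietary interventions twice each for four total intervention periods". Section {14} sets the size: "therefore enroll *n* = 22 eligible individuals to have *n* = 20 individuals complete the trial". Outcomes {12} classes the microbiota outcomes as exploratory, while Objectives {7} poses a hypothesis of beneficial change in diversity and community composition, both over time and against the Western diet.

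**The concern.** Depth adjustment exists because a sample with more reads shows higher counts of everything. The unit that has a depth is the sample. A total per subject is one number shared by all five samples of a person. The contrasts of interest, after versus before a period and mini-MED versus Western, compare samples of the same person, so that number cannot enter them. Sample-to-sample depth differences would stay in the data as noise. If depth differed systematically between diets or visits, they would be read as a diet effect.

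The PERMANOVA raises a related point. For diet there are no separate groups of people, since everyone is in both. If repeated samples are pooled and labels permuted freely, stable differences between people enter the null distribution of a within-person contrast. At stake is the microbiome hypothesis in Objectives {7}. The primary outcome is not affected.

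**Working it through.** The protocol gives no power or effect size for the microbiome, so there is no figure of its own to reproduce. From the protocol: 20 completers, 5 stool samples each, 4 of them post-period (2 per diet). Everything else below is an assumption, shown as a range.

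**1. Depth term.** For person i and sample t, with true depth d_it:

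log E(Y_it) = b_i + β·diet_it + log d_it

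Replace log d_it by γ·D_i, where D_i is a per-subject total. The difference between two samples of one person then contains γ·D_i − γ·D_i = 0, and log d_it − log d_is remains unadjusted. With within-person SD s_w of log counts and s_d of log depth:

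- Variance factor: V = (s_w² + s_d²)/s_w²
- Power, if per-sample adjustment gives 80% at two-sided 0.05: Φ[(1.960 + 0.842)/√V − 1.960]

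| s_w | s_d | V | Power |
|---|---|---|---|
| 1.0 | 0.2 | 1.04 | 78% |
| 0.8 | 0.3 | 1.14 | 75% |
| 0.8 | 0.5 | 1.39 | 66% |
| 0.5 | 0.5 | 2.00 | 51% |
| 0.5 | 0.7 | 2.96 | 37% |

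Third row in full: (0.64 + 0.25)/0.64 = 1.39; 2.802/1.179 − 1.960 = 0.416; Φ = 0.66.

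**2. PERMANOVA on pooled samples, diet effect.** Simulation: 20 participants × 4 post-period samples, 20-dimensional Gaussian data, Euclidean distance, 199 permutations, 400 replicates, alpha 0.05. The shift is the total length of the mean difference over the 20 dimensions, in units of the within-person SD of one dimension. ICC is the share of variance explained by participant. Each cell gives free / within-participant permutation, in % rejecting.

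| ICC | No effect | Shift 1.0 SD | Shift 2.0 SD |
|---|---|---|---|
| 0.2 | 0.5 / 6.5 | 46.8 / 77.5 | 100 / 100 |
| 0.3 | 0 / 4.2 | 30.2 / 77.0 | 100 / 100 |
| 0.5 | 0 / 7.2 | 4.0 / 77.8 | 97.8 / 100 |
| 0.7 | 0 / 6.0 | 0 / 76.5 | 27.2 / 100 |
| 0.8 | 0 / 4.0 | 0 / 75.8 | 0.2 / 100 |
| 0.9 | 0 / 5.0 | 0 / 76.8 | 0 / 100 |

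The Monte Carlo standard error at a 5% rate is √(0.05·0.95/400) = 1.1 points, so the restricted null rates are compatible with 5%. At ICC 0.2 and a 1.25 SD shift the pair is 81.8 / 95.5. A second simulation gave free-permutation power of 42%, 1.5% and 0% at ICC 0.2, 0.5 and 0.7 for a 1.0 SD shift, against 74% to 79% restricted.

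**3. PERMANOVA on pooled samples, a between-person factor such as intervention order.** The error reverses. Free permutation rejects a true null in 45% of runs at ICC 0.2, rising to 98% at ICC 0.9. Permuting whole participants gives 5% to 6%.

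**The case against.** The strongest reply has four parts.

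- **The models are built for repeated samples.** A reader might infer that the microbiome analyses ignore the five samples per person. The text does not support that. The sentence on taxa and genes names mixed effects regression, the next names LMMs, and {20a} uses a random intercept for repeated measures elsewhere. This part of the reply stands in full.
- **The per-subject phrase may be loose wording for the sample's own library size**, since the next sentence drops it. That is plausible. It leaves two readings, of which only the per-sample one works, so the text still needs correcting. The plan states no scale for the covariate, so it cannot be faulted for using an untransformed count. A log-depth covariate with free slope contains the offset as the case of slope 1, so choosing between them is a preference.
- **Free permutation of pooled samples is nowhere stated.** The scheme is a detail that an article may leave to the full plan. A comparison at week 4 by first diet uses one sample per person, and unrestricted permutation is then valid. This stands, and it is why the PERMANOVA point is conditional.
- **The outcomes are exploratory**, with no power claimed for them. This stands and limits the weight of the point.

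**Conclusion.** The depth term as written is wrong for the contrasts that it serves. That follows from the design alone, without any assumed figure. Its size is uncertain: a variance factor of 1.04 to 2.96 over the assumed SDs. Bias arises only if depth differs systematically by diet or visit, and nothing in the protocol indicates that it does.

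The PERMANOVA point holds conditionally. If repeated samples are pooled and permuted freely, the diet test is conservative (0% to 0.5% null rejection), and power for moderate shifts is low at an ICC of about 0.5 or more. A reader might go further and say that the test has almost no power for diet. The documents do not support that: they give neither an ICC nor an effect size, and free permutation still reaches 82% at ICC 0.2 with a 1.25 SD shift and 98% at ICC 0.5 with a 2.0 SD shift. The simulations use Euclidean distance on Gaussian data and omit the baseline sample, so they show direction and rough size, not values for UniFrac or Bray–Curtis. The consequence is confined to the exploratory microbiome outcomes and the hypothesis attached to them in Objectives {7}.

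**What to change.** In {20a}:

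1. Replace the per-subject count by the log total sequence count of each sample, as an offset or as a log-depth covariate, and name a participant random intercept in the negative binomial model.
2. Use the same per-sample definition in the LMMs with cardiometabolic indicators.
3. State which samples enter the PERMANOVA. If repeated samples are pooled, permute diet labels within participant; if intervention order is tested, permute whole participants. Otherwise use one sample per person.

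The cost is a few words and code options. No data collection changes, and stool is stored for batch analysis at study completion.
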